**Protocol Revision Record**

| **Version Number** | **Version Date** |
| --- | --- |
| V1.0 | July 20, 2022 |
| V1.1 | September 6, 2022 |
| V1.2 | September 22, 2022 |
| V1.3 | January 9, 2023 |

**CLINICAL STUDY PROTOCOL SYNOPSIS**

| **Protocol title** | Endovascular Denervation (EDN) for the Treatment of Type 2 Diabetes Mellitus |
| --- | --- |
| **Objective** | To evaluate the safety and efficacy of EDN at celiac and hepatic arteries in patients with type 2 diabetes who have inadequate glycemic control |
| **Study Design:** | This is a multicentre, open-label, single-arm intervention study with 37 patients with type 2 diabetes who have suboptimal or poor glycemic control (i.e., glycated haemoglobin (HbA1c >7.5% and <10.5%) on two to four antidiabetic drugs, including metformin)  The study has 4 distinct stages, as follows.  **Stage 1:** Screening  HbA1c will be confirmed during screening along with additional parameters of eligibility  **Stage 2:** Run-in period  A 14-day run-in period will be included to conduct continuous glucose monitoring (CGM) and collect other parameters.  **Stage 3:** Treatment  Each patient will undergo EDN. Discrete radiofrequency ablations at 60 ℃, each lasting up to 120 seconds will be applied to obtain at least 18 ablations, with a maximum of up to 6 electrodes delivering energy simultaneously during each session. Ablations will be performed at the celiac, common hepatic and proper hepatic arteries  **Stage 4:** Follow-up  Patients will be followed up at 1, 3, 6, 12, and 24 months for AEs, laboratory tests and other parameters |
| **Data Management** | The data management of this trial will be undertaken by a Contract Research Organization (CRO). The data management process shall comply with the relevant regulatory requirements for data management and follow the standard operating procedures (SOPs) of the data management department to ensure the authenticity, accuracy, integrity, and reliability of the clinical trial data. |
| **Number of Subjects**  **Planned** | Approximately 30 patients will be treated with EDN. Replacement subjects may be added if subjects are screen failures or withdraw prior to drug product infusion. |
| **Inclusion Criteria** | - Age of 18–65 years old (both inclusive) - Understand the requirements and treatments of the trial, agreed to and were able to complete all follow-up assessments required for the trial, and signed informed consent before any special trial-related tests and treatments were performed - Diagnosed with T2DM for ≥1 and <15 years (according to WHO criteria) - Metformin (daily dose ≥1000mg) was combined with 1-3 oral antidiabetic drugs (OADs) for more than 3 months and/or insulin (no dose limit). Specific OADs were: insulin secretagogues (sulfonylureas/glinides), thiazolidinediones and α-glucosidase inhibitors, and the combined OADs were at least half of the maximum approved dose in the package insert - Glycosylated hemoglobin of 7.5–10.5% (58–91 mmol/mol) (both inclusive) - Body mass index of 18–40 kg/m^2^ (both inclusive) |
| **Exclusion Criteria** | - Type 1 diabetes, late-onset autoimmune diabetes in adults (LADA), or any secondary diabetes. - Previous aortic disease (e.g., aortic aneurysm or dissection) or aortic surgery (including celiac artery denervation). - Baseline CTA showing aortic aneurysm or dissection, anatomical abnormalities of the hepatic artery and its branches, or other abnormal vascular structure/status (e.g., severe tortuosity or stenosis of the artery, intravascular thrombus, or unstable plaque) deemed unsuitable for vascular ablation by the investigator. - More than two self-reported or documented episodes of severe hypoglycemia in the past 6 months (defined as hypoglycemia with severe cognitive impairment requiring assistance from another person). - More than one documented episode of hyperglycemia requiring hospitalization in the past 6 months, including diabetic ketoacidosis or hyperosmolar coma. - Severe diabetic complications, such as retinal, renal, vascular, neuropathy, or diabetic foot, deemed ineligible for enrollment by the investigator. - Major cardiovascular and cerebrovascular events (MACCE) within the past 6 months, including cerebrovascular accident (CVA), transient cerebral ischemia (TIA), heart failure (NYHA class III-IV), acute myocardial infarction, or unstable angina requiring hospitalization (including previous coronary artery bypass grafting or coronary stent implantation); and uncontrolled or severe arrhythmias. - Severe autonomic neuropathy (orthostatic hypotension, gastroparesis syndrome, etc.). - Untreated or uncontrolled high blood pressure (SBP ≥ 160 mmHg or DBP ≥ 100 mmHg), or low blood pressure (BP < 90/50 mmHg). - History of renal insufficiency or failure with baseline estimated glomerular filtration rate (eGFR) < 60 mL/min/1.73 m² (see Note C of the Clinical Data Collection Table in Table 5-2 for the eGFR formula). - Chronic active hepatitis, severe hepatobiliary disease (including cirrhosis), or hepatic insufficiency (alanine and/or aspartate aminotransferase > 3 times the upper limit of normal or serum total bilirubin > 2 times the upper limit of normal). - Acute or chronic pancreatitis during screening and baseline periods. - Acute systemic infections during screening and baseline periods. - Bleeding tendency or coagulopathy (PT, APTT, or INR > 2 times the upper limit of normal; platelet count < 80×10⁹/L or ≥ 700×10⁹/L). - Active GI ulcer or GI bleeding within 3 months before baseline. - Symptomatic cholelithiasis (including cholecystolithiasis, extrahepatic bile duct stones, and intrahepatic bile duct stones) without effective treatment such as cholecystectomy, choledocholithotomy, internal drainage, or external drainage. - Hyperthyroidism, hypothyroidism, acromegaly, Cushing's syndrome, or other endocrine and metabolic diseases. - Autoimmune diseases. - Diagnosed with a high risk of malignancy or cancer development/recurrence, or expected life expectancy < 12 months. - Major surgical procedures within the past 3 months. - Conditions or concomitant medical conditions, such as hemoglobinopathy or hemolytic anemia, preventing the primary endpoint from being assessed. - Mental illness preventing cooperation. - Treatment with a GLP-1 receptor agonist, DPP-4 inhibitor, or SGLT-2 inhibitor within 3 months before the screening period. - Systemic or intra-articular glucocorticoids (other than topical, inhaled, or eye drops) within 3 months before the screening period. - Use of weight-loss medications such as orlistat or other treatments for weight loss (weight-loss tea/herbal medicine/acupuncture, etc.) within 3 months before the screening period. - Prior or anticipated bariatric surgery such as subtotal gastrectomy or liposuction. - Use of central sympathetic inhibitors or anticonvulsants within 3 months prior to or anticipated during the screening period. - Long-term anticoagulation therapy requiring preoperative heparin bridging anticoagulation that is not possible. - Weight gain of more than 10% in the past 3 months. - Allergy to or contraindication to contrast media, with inadequate pretreatment as judged by the investigator. - Known history of allergy to the study device (containing polytetrafluoroethylene or Nitinol) or medications associated with the trial protocol. - Participation in other clinical studies within 3 months before enrollment. - Anticipation of participation in a clinical trial of another drug or medical device within 24 months after baseline surgery. - Pregnancy or lactation, or plans to become pregnant within the next 2 years (all women of childbearing age must undergo a pregnancy test within 7 days before baseline surgery). - Drastic changes in diet and exercise habits expected during the study (due to religious/work needs/weight loss, etc.). - Irregular day and night work (night shift workers). - History of alcohol, drug, or substance abuse. - Scheduled periodic blood product therapy or severe blood loss during the previous 3 months/study period. - Any condition, as judged by the investigator, that affects the safety of the participant or interferes with the evaluation of the test results. - Aortic aneurysm or aortic dissection confirmed on angiography before the procedure.   Vascular structure and conditions deemed unsuitable for ablation (e.g., severe tortuosity or stenosis of the artery, abnormal vascular anatomy, thrombus, or unstable plaque). |
| **Endpoints** | **Primary Endpoints:**   - The occurrence of composite major adverse events (MAE) related to the device and/or the procedure within 30 days post-procedure. MAE includes the following events:  1. Hypoglycemic or hyperglycemic events requiring hospitalization 2. Vascular complications requiring surgical repair, interventional treatment, thrombin injection, or blood transfusion 3. Celiac/hepatic artery dissection or perforation requiring intervention 4. Significant embolic events leading to end-organ damage or requiring intervention to prevent end-organ damage 5. Acute liver dysfunction or liver failure 6. All-cause mortality  - The change in glycated hemoglobin (HbA1c) at 6 months post-procedure compared to baseline levels.   **Secondary endpoints:**   - The changes of Hba1c from baseline at 1, 3, 12 and 24 months post procedure - The changes of assessment of β-cell function and insulin resistance (Homeostatic Model Assessment for β-cell function and insulin resistance, HOMA-β/HOMA-IR) - The changes of mean glucose, postprandial glucose increase, nocturnal glucose increase and time in range (TIR, 3.9-10.3 mmol/L) by 14 - day continuous glucose monitoring (CGM) - The changes of blood lipids (triglycerides, total cholesterol, high- and low-density lipoprotein) - The changes of liver function (alanine aminotransferase, aspartate aminotransferase, alkaline phosphatase and gamma - glutamyl transferase) - The changes of renal function (urea nitrogen, blood creatinine and eGFR) - The changes of glucose, insulin and C - peptide in oral glucose tolerance test (OGTT) - Proportion of patients achieving target HbA1c (< 7.0% and ≤6.5%) - Proportion of patients with HbA1c < 7% without hypoglycemia/severe hypoglycemia or weight gain - Proportion of patients with the changes of in type/dose of antidiabetic drugs - Incidence of hypoglycemia and severe hypoglycemia (blood glucose level < 3.9 mmol/L) - The occurrence of new significant celiac or hepatic artery stenosis at 6 months post procedure (stenosis >50% as assessed by CT angiography and confirmed by digital subtrationsubtraction angiography when CT angiography assessment shows abnormal) - The occurrence of device and/or procedure-related adverse events and serious adverse events - Incidence of cardiovascular and cerebrovascular complications (defined as cardiovascular death, myocardial infarction and ischemic stroke) - Quality of life assessment (EQ-5D-5L) |
| **Statistical Methods** | **Sample size estimation:**  No formal sample size calculation was performed. However, the sample size of 30 (treated) was determined based on the hypothesis that patients would experience a reduction in HbA1c at 6 months. To achieve a predefined 1.0% reduction in HbA1c, with a standard deviation of 1.5%, a sample size of 26 would be required to yield a lower two-sided 95% confidence bound of approximately 0. Taking into account a 10% drop out rate, the estimated sample size is 29.  **Populations for analysis:**  Baseline characteristics were analyzed in all enrolled patients. The treated patients were analyzed for safety profile, and patients with follow-ups were analyzed for efficacy.  **Analysis of primary endpoints:**  All adverse events were recorded by and assessed by all investigators for the association with the device or procedure. HbA1c reductions at 6 months were measured for patients with 6-month follow-up and expressed as mean with a 2-sided 95% CI.  The success criterion for this study is defined as no device- or procedure-related MAE occured and achievement of HbA1c reduction at 6 months. |

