#### **5.2.3.2 Withdrawal**

Although withdrawal without cause is discouraged, subjects may withdraw from the clinical trial at any time, with or without explanation, and this will not affect their future medical care.

The investigator may also discontinue or withdraw a subject from the study for the following reasons:

Occurrence of an unanticipated adverse device effect (UADE) that poses significant or unreasonable risk to the subject.

- Any condition arising during the trial that could harm the subject (e.g., pregnancy, inability to continue follow-up assessments, hypersensitivity to the study device or contrast medium).

Inability of the subject to complete the required study procedures or follow-up.

- All subjects enrolled in the trial (including those who withdraw or are lost to follow-up) will be documented. Withdrawn subjects will not be replaced, and no additional follow-up will be conducted. Investigators should document the reason for withdrawal whenever possible.
- If withdrawal is related to the safety or efficacy of the study device or procedure, the investigator should seek subject consent to continue clinical monitoring outside the trial. Data collected prior to withdrawal will be retained and included in analyses, but no further data will be collected after withdrawal.

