#### **5.2.3.3 Enrollment Control**

The study will enroll at least 30 subjects, with no restrictions on the number of subjects recruited at each participating center.

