## 5.4 Study Flow

### 5.4.1 Study Flowchart

This feasibility clinical study of endovascular denervation for T2DM will recruit up to 30 subjects across a maximum of three centers in mainland China.

**Enrollment period:** approximately 3 months.

**Follow-up period:** 24 months.

All subjects will be screened according to inclusion and exclusion criteria and enrolled in a non-randomized manner.

Clinical follow-up visits will be conducted at the following time points:

Day 7 post-procedure or before discharge (whichever comes first), 30 days (±7 days), 3 months (±14 days), 6 months (±30 days), 12 months (±30 days), and 24 months (±30 days) post-procedure.

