**Data Analysis**

As a single-arm feasibility study, no formal hypothesis testing is planned. Descriptive statistics will summarize baseline demographics, safety endpoints, and other categorical data for all enrolled subjects. For efficacy endpoints, paired t-tests will be used to compare post- vs. pre-procedure HbA1c (%) and other continuous outcomes, and the one-sided 97.5% lower confidence limit of the mean difference will be calculated.

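### The sample-size sentence misdescribes its criterion (26 patients give a lower 95% bound of about 0.39, not about 0) and states no power, and the planned size is given inconsistently

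*Protocol*

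**What the plan says.** The only derivation of the sample size is under Statistical Methods in the Clinical Study Protocol Synopsis. It first disclaims a formal calculation and then gives one. Its inputs are "To achieve a predefined 1.0% reduction in HbA1c, with a standard deviation of 1.5" per cent, and its criterion is that "a sample size of 26 would be required to yield a lower two-sided 95% confidence bound of approximately 0". A 10% dropout allowance takes 26 to 29, and the chosen size is 30 treated. No power appears anywhere in the protocol. Section 6.3 gives 30 without a derivation. The Protocol Synopsis and Section 6.2 say there is no formal hypothesis, and Section 6.4 says no formal testing is planned. Section 6.4 nevertheless specifies paired t-tests and says that "the one-sided 97.5% lower confidence limit of the mean difference will be calculated".

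The planned size is stated as follows:

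- Clinical Study Protocol Synopsis, Study Design: "single-arm intervention study with 37 patients with type 2 diabetes".
- Same synopsis, number of subjects and Statistical Methods: about 30 treated, and 30 treated.
- Protocol Synopsis, Section 5.2 and Section 6.3: 30.
- Section 5.2.3.3: "The study will enroll at least 30 subjects".
- Section 5.4.1: "will recruit up to 30 subjects across a maximum of three centers".
- Figure 5-1, text at the EDN step: N = 10.

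**The concern.** The sentence gives a mean, an SD, a sample size and a resulting confidence bound. Three of these fix the fourth, and the stated bound does not follow from the other three. A reader cannot tell whether the trial was sized for precision (an interval of a given width) or for power (a given chance that the interval excludes zero). Nor can a reader see what precision to expect at 6 months.

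The size statements matter because the trial is open-label and the synopsis defines success partly as no device- or procedure-related major adverse event. The chance of meeting that condition falls with each patient treated, so the number treated should be fixed. A minimum in one section and a maximum in another do not fix it.

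**Working it through.** **Inputs.** Mean reduction 1.0, SD 1.5, n = 26, two-sided 95% and dropout 10% all come from the Clinical Study Protocol Synopsis. The paired analysis comes from Section 6.4; its one-sided 97.5% lower limit is the same number as the lower limit of a two-sided 95% interval. The protocol does not say what the 1.5 refers to. I assume it is the SD of the change from baseline.

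**The sentence as written.** Lower bound = mean − t(0.975, n−1) × SD/√n. At n = 26, SD/√n = 1.5/√26 = 0.294 and t = 2.060. The half-width is 0.606 and the interval is 0.39 to 1.61.

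| n | half-width | lower bound | power, paired t-test, two-sided 5% |
|---|---|---|---|
| 10 | 1.073 | −0.07 | 47% |
| 11 | 1.008 | −0.01 | 51% |
| 12 | 0.953 | 0.05 | 56% |
| 26 | 0.606 | 0.39 | 90.4% |
| 30 | 0.560 | 0.44 | 94% |
| 37 | 0.500 | 0.50 | 98% |

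A bound of about 0 therefore belongs to 11 or 12 patients.

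**Other readings of the same sentence at n = 26.** A normal quantile gives 0.42. A one-sided 95% bound gives 0.50. If 1.5 were a single-visit SD with zero correlation between visits, the SD of the change would be 1.5 × √2 and the bound 0.14. None is about 0. For the bound to be 0 at n = 26, the SD of the change would have to be 2.48, or the observed mean 0.61.

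**Where 26 can come from.** Add a power requirement, which the protocol does not state. The noncentrality is 1.0/0.294 = 3.40. The smallest n for a two-sided 5% paired t-test is 20 for 80% power, 23 for 85%, 26 for 90% and 32 for 95%. At n = 25 power is 89.2%; at n = 26 it is 90.4%. A simulation of 400,000 trials of 26 patients agrees: the lower bound exceeds 0 in about 90.5% of them, and its 10th percentile is about 0.01. The bound is thus about 0 at the unlucky end of its distribution, not at its expected value. The match is not unique: 26 is also the smallest n for 95% power at one-sided 5% (95.2%), though that does not fit the stated two-sided 95% bound.

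**Dropout.** 26/0.9 = 28.9, rounded up to 29. This reproduces. Thirty treated less 10% leaves 27 evaluable, with power 91.5% on the same assumptions.

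**Planned size.** At least 30 and up to 30 agree only at exactly 30. N = 10 agrees with none of the others. Section 5.2.3.1 places enrolment at introduction of the catheter, which leaves little room for 37 enrolled against 30 treated, and the protocol does not say that 37 counts a different set.

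**Effect on the safety part of the success rule.** The protocol gives no expected event rate. Purely for illustration, with a true rate of related major events of 1%, the chance of none is 90% at 10 patients, 74% at 30 and 69% at 37. At 3% it is 74%, 40% and 32%.

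**The case against.** The strongest defence is that 26 is not an error. It is exactly the paired t-test size for 90% power at two-sided 5%, and 29 follows from it. The criterion is still the lower 95% bound compared with 0; only the probability of clearing it was left out. That stands, and it means the number should not be called wrong.

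It is also fair that this is a feasibility study with no formal hypothesis and no interim analysis for efficacy or futility, and that Section 6.3 and four other places agree on 30. The N = 10 survives only as loose text from a flowchart, so it is weak evidence of a rival target. These points limit the weight of the finding. They do not make the sentence correct, and they do not reconcile 37, or a floor with a ceiling.

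Two stronger inferences are not supported. A reader might conclude that the trial is mis-sized; on the stated inputs, 26 evaluable patients are ample for the bound described. A reader might also see a contradiction between the synopsis, which allows replacement of some subjects, and Section 5.2.3.2, which says "Withdrawn subjects will not be replaced". The synopsis covers screen failures and withdrawals before treatment. Section 5.2.3.2 concerns enrolled subjects, and enrolment is at catheter introduction. The two rules are compatible. Only the synopsis cut-off, which refers to infusion of a drug product in a device trial, needs rewording.

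**Conclusion.** The concern holds in this form: the only sample-size derivation misdescribes its criterion and omits the power that would explain it. The expected lower bound at n = 26 is about 0.39 (half-width about 0.61), not about 0. This rests on 1.5 being the SD of the change; under the zero-correlation single-visit reading the bound is 0.14, still not about 0. The 90% power is inferred from the arithmetic, not from the text, so only the sponsor can confirm it. The planned-size statements also conflict and need to be reconciled. Neither defect changes an endpoint, an analysis or the number of patients required, so this is a wording-level correction.

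**What to change.** 1. In the Clinical Study Protocol Synopsis, replace the criterion with one of the following.
   - Precision: with 26 evaluable subjects and an SD of the change of 1.5, an observed mean reduction of 1.0 has a two-sided 95% lower bound of about 0.39 (half-width about 0.61).
   - Power, only if the sponsor confirms that this was the basis: 26 evaluable subjects give about a 90% chance that the lower two-sided 95% bound exceeds 0 if the true mean reduction is 1.0 and the SD of the change is 1.5. In that case, also align the sentence disclaiming a formal calculation and the no-hypothesis statements in the Protocol Synopsis and Sections 6.2 and 6.4, so that the document does not both use and deny a power basis.
2. State that 1.5 is the SD of the change in HbA1c from baseline.
3. Give one fixed number of treated subjects. Correct 37 in the Clinical Study Protocol Synopsis, the minimum in Section 5.2.3.3, the maximum in Section 5.4.1 and N = 10 in Figure 5-1 to agree with the 30 in the Statistical Methods of that synopsis, the Protocol Synopsis, Section 5.2 and Section 6.3. If 37 counts a different set, name the set.
4. Reword the replacement cut-off in the Clinical Study Protocol Synopsis in terms of the device procedure. Section 5.2.3.2 can stay as it is.

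The cost is protocol wording only, with no extra patients and no change to endpoints or analysis.

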# Study Design

## 5.1 Overall Design and Rationale

The feasibility clinical trial of endovascular denervation for the treatment of T2DM is a prospective, multicenter, single-arm feasibility study. The study will employ the EDN system (including generator and catheter) developed by Shanghai Brattea Medical Technology Co., Ltd. to perform EDN in the celiac trunk and hepatic artery for T2DM treatment.

As this is an early feasibility study of EDN for T2DM, and no device with the same indication has yet been approved for registration in China, a single-arm design was selected. Additionally, the primary study endpoints are not significantly influenced by placebo effects or psychological factors, making this design appropriate.

During EDN, anticoagulation will be administered according to clinical standards. Antiplatelet therapy will be used pre- and post-procedure to prevent thrombosis. Dynamic safety monitoring will be conducted throughout the trial to minimize patient risk. All enrolled subjects who undergo EDN will be followed for 24 months post-procedure.

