#### 5.4.7.2 Concomitant Antidiabetic Therapy and Lifestyle Management

Subjects must be on stable OAD therapy for at least 3 months prior to the baseline procedure (subjects taking α-glucosidase inhibitors must undergo a 2-week washout before enrollment). After EDN, OADs and insulin regimens will be adjusted by the investigator according to blood glucose levels and guideline recommendations (see Sections 5.4.7.3 and 5.4.7.4). All changes in OADs and insulin type/dose must be documented at follow-up visits.

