**Study Period Criteria (≥2 weeks of 4-point SMBG daily mean):**

- 4 weeks post-EDN: FBG ≥ 13.9 mmol/L
- 8 weeks post-EDN: FBG ≥ 11.1 mmol/L
- 8 weeks post-EDN: HbA1c ≥ 8.5%

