## 6.4 Statistical Methods

**Statistical Analysis Sets**

Primary, secondary, and additional endpoints will be analyzed using both the Intent-to-Treat (ITT) and Per-Protocol (PPS) populations.

ITT: All subjects who signed written ICF and were enrolled, regardless of whether EDN was successfully performed.

PPS: Subjects who underwent EDN in the celiac/hepatic arteries using the investigational device.

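### The primary HbA1c analysis does not separate EDN from glucose-lowering treatment intensified after it, and the synopsis and section 6.4 name different efficacy populations

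*Protocol*

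**What the plan says.** **Primary analysis.** The synopsis (Statistical Methods) states: "HbA1c reductions at 6 months were measured for patients with 6-month follow-up and expressed as mean with a 2-sided 95% CI". It also limits efficacy to patients who have follow-up, and defines success as no device- or procedure-related major adverse event together with an HbA1c reduction at 6 months. It sets no minimum reduction and no condition on medication. Section 6.4 (Data Analysis) uses a paired t-test of post- against pre-procedure HbA1c.

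**Populations.** Section 6.4 analyses the primary endpoints in two sets. One is "ITT: All subjects who signed written ICF and were enrolled, regardless of whether EDN was successfully performed". The other, PPS, is everyone who underwent EDN in the celiac or hepatic arteries with the device. Neither set depends on medication or on attending month 6.

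**Treatment before the reading.** Section 5.4.7.2: "After EDN, OADs and insulin regimens will be adjusted by the investigator according to blood glucose levels and guideline recommendations". Section 5.4.7.3 lets investigators add insulin to existing treatment for hyperglycemia without an identified cause. Two triggers use fasting glucose, at 4 and 8 weeks; the third is "8 weeks post-EDN: HbA1c ≥ 8.5"%. Section 5.2.3.2 does not list rescue as a reason for withdrawal.

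**Design.** Section 5.4.3 confirms that there is no control group. Section 5.1 justifies this partly because "the primary study endpoints are not significantly influenced by placebo effects or psychological factors"; it does not discuss drug intensification. Drug changes are recorded (section 5.4.7.1) and form a secondary endpoint (section 5.3.2), but nothing links them to the primary analysis.

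**The concern.** In a controlled trial, rescue in both arms can be compared. Here the only contrast is each patient's month-6 value against baseline, so whatever lowers HbA1c in between enters the estimate. One rescue trigger is a high value of the endpoint variable itself, so the patients most likely to receive added insulin are those whose HbA1c did not fall enough after EDN. Their later improvement is then averaged into the EDN result, and the success criterion has no size or medication condition to offset this.

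The second issue is who is counted. A result limited to 6-month attenders and an ITT result on all enrolled subjects are different estimates, and the protocol calls for both without saying which one the success criterion uses.

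**Working it through.** **1. The plan's own figures.** Inputs from the synopsis: "To achieve a predefined 1.0% reduction in HbA1c, with a standard deviation of 1.5"%, 26 evaluable patients, 10% dropout. A paired t-test at two-sided 5% gives 90.4% power with n = 26, and 26/0.9 = 28.9, rounded up to 29. So 26 and 29 reproduce as a 90%-power calculation, although the synopsis states no power and says "No formal sample size calculation was performed". As worded ("a sample size of 26 would be required to yield a lower two-sided 95% confidence bound of approximately 0") they do not reproduce: 1.0 − 2.06 × 1.5/√26 = 0.39. The half-width, 2.06 × 1.5/√26 = 0.61, is the observed mean reduction needed for the lower bound to clear 0 when the SD is 1.5.

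**2. How many could meet the HbA1c trigger.** Entry range 7.5 to 10.5% (section 5.2.1). Assume baseline is uniform over that range. With no change in anyone, (10.5 − 8.5)/3 = 67% are at or above 8.5%; after a full 1.0-point fall in everyone, (9.5 − 8.5)/3 = 33%. Letting the month-3 change vary with SD 1.5 around zero gives about 61%.

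**3. Spurious mean reduction.** If EDN does nothing, a rescued share r and a drug effect D (0.5 to 1.0 points, assumed) shift the mean by r × D.
- All qualifiers rescued: 0.61 × 0.5 ≈ 0.31; 0.61 × 1.0 = 0.61.
- Half rescued: 0.305 × 0.5 ≈ 0.15; 0.305 × 1.0 ≈ 0.31.

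**4. What this does to the confidence bound.** Simulation: n = 26, no EDN effect, SD of change 1.5, month-3/month-6 correlation 0.7, rescue decided on the month-3 value, full drug effect by month 6.

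| Rescued | Lower 95% bound above 0 (nominal 2.5%) |
|---|---|
| All qualifiers | about 19–62% |
| Half of qualifiers | about 8–18% |

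Simulation details move the ends by a point or two. Across these settings the mean shows some reduction in about 71–99% of trials. With no EDN effect and no rescue, that share would be 50% by symmetry.

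**5. Check without the trigger model.** Fix r and D, and add the mixture variance: SD = √(1.5² + r(1 − r)D²). For r = 0.4, D = 1.0: SD = √(2.25 + 0.24) = 1.58, noncentrality 0.4 × √26/1.58 = 1.29, and the bound exceeds 0 in 24% of trials. For r = 0.2, D = 1.0: SD = √(2.25 + 0.16) = 1.55, and 9.2%.

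**6. Attenders against all enrolled.** If 26 of 29 attend with mean reduction 1.0 and the other 3 did not change, the all-subject mean is 26 × 1.0/29 = 0.90. If those 3 worsened by 0.5 or 1.0, it is 0.84 or 0.79. This effect is smaller than the rescue effect at the upper settings above.

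**The case against.** **The protocol never says that post-rescue values are counted; the SAP may hold a rule.** It is true that no sentence says so, and an unseen SAP could add rules for rescue and missing values. But the protocol already fixes the variable, populations, test and success criterion. Followed as written, rescued patients stay in every named set and their month-6 value enters. The conflict between the synopsis and section 6.4 lies within the protocol. A reader might go further and infer that section 6.4's paired t-test rules out a true ITT analysis. It does not say that: imputation could be specified elsewhere.

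**This is a feasibility study with no hypothesis.** Sections 6.2 and 6.4 say so, and the success criterion is not a confidence bound above 0. The percentages in step 4 therefore show how far the interval can mislead; they are not the error rate of a declared test. The synopsis nonetheless sets a success criterion, and a descriptive mean also needs a clear meaning.

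**The rescue assumptions are high.** Rescue is discretionary, so rescuing every qualifier is an upper case. The visit windows (+14 days at month 3, −30 at month 6) can shorten a nominal gap of about 91 days to 91 − 14 − 30 = 47 days, so a full drug effect by the reading is not assured. This stands.

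**Bias can run the other way.** Stepwise drug reduction after hypoglycemia (section 5.4.7.4) would understate EDN. This also stands; hyperglycemia-triggered rescue, however, favors EDN.

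**Discarding post-rescue values is fragile.** If 61% were rescued, about 26 × 0.39 ≈ 10 month-6 values would remain. This argues against making such an estimate the sole primary result, but not against reporting it beside the all-values estimate.

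**Conclusion.** The point holds and should be fixed. As stated, the primary analysis and success criterion measure EDN plus whatever intensification follows, and the efficacy population is described in two incompatible ways. With no EDN effect, rescue alone could give a mean reduction of about 0.15 to 0.61 points, against a planned 1.0. This rests on an assumed uniform baseline, rescue of half to all qualifiers, a drug effect of 0.5 to 1.0 points and, for the interval results, a correlation of 0.7. Only the SD of 1.5 and n = 26 come from the protocol. The actual size cannot be computed from the documents.

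A reader might infer that the trial cannot inform efficacy at all. The documents do not support that. HbA1c at 1 and 3 months and drug changes are prespecified secondary endpoints, and the month-3 value largely precedes HbA1c-triggered rescue, although glucose-triggered rescue and routine adjustment can come earlier. Nor do they support larger false-signal rates based on a smaller SD: 1.5 is the only SD the protocol gives.

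**What to change.** In the synopsis (Statistical Methods) and section 6.4:

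1. Use one efficacy population: all enrolled subjects, as in section 6.4's ITT definition. Remove the synopsis restriction to patients with follow-up. Analyse the baseline, 1-, 3- and 6-month HbA1c already collected, for example with a repeated-measures model, so that subjects without a month-6 value still contribute.
2. Beside the all-values estimate, prespecify a second one that sets aside HbA1c measured after rescue insulin or after a glucose-lowering drug is added or increased. Define the threshold for an increase so that minor insulin titration does not count. Values after drug reductions stay in.
3. Report the number of subjects intensified by month 6, and attribute an HbA1c reduction to EDN only if the two estimates agree.

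The cost is protocol and SAP wording plus a modest amount of analysis; the visits and drug-change records already exist. The reduction attributable to EDN may turn out smaller and less precise. No change to the rescue rules is proposed.
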